### Intervention Package

#### Counseling Group

In this group, after the children have been examined, a treatment plan and follow-up schedule will be advised by the pediatric ophthalmologist to the parents or guardians along with the child. The parent or guardian and the child will receive counseling from a trained counselor (SK) as per the set counseling protocol in every follow-up visit where the disease-specific leaflet will be used as a counseling tool, a copy of which will also be handed over to them. A counseling protocol for the common ocular conditions has been designed by the research team. The counselor will be oriented and trained as per the counseling protocol a week before the participants are enrolled in the study. Children, along with their parent or guardian, will be receiving counseling irrespective of patient age, parental education, ocular conditions, and other factors. If more than one guardian or both mother and father are accompanying the child, both will be included in the counseling session. The counselor will deliver verbal counseling for all participants in all follow-up visits irrespective of the ocular conditions and other factors. The counseling session for all participants will last for 20 minutes.

#### SMS Text and Phone Call Reminder Group

In this group, after the children have been examined and a treatment plan and the follow-up have schedule been advised, they will be discharged from the department. They will receive an SMS text 3 days prior to and a phone call 1 day prior to their scheduled follow-up visits. Text messages will be sent until it is confirmed that the sent message has been received. In the case of message delivery failure, it will be sent again 3 more times to ensure successful delivery. If the SMS text is not delivered after 3 attempts, then a message will be sent to the next phone number (if available) as recorded in the proforma during the interview. A phone call will be deemed to be completed once it is received by the respondent; calls will be repeated at least 3 times if the phone is not answered in the first instance. If the call is not answered even after 3 attempts, the participant will be excluded from the study.

The assistant (DA) will be responsible for making the reminder SMS and calls, making the records, and tracking the follow-up patients. The standard text and the call format have been developed in the local language (Nepali).

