## Methods

### Study Design and Setting

This public health intervention study will be conducted at Hiralal Santudevi Pradhan Institute of Ophthalmic Sciences which includes 13 satellite clinics and 1 base hospital (Bharatpur Eye Hospital [BEH]). The study participants will be enrolled only from the pediatric department of BEH, a centrally located tertiary eye hospital in the Chitwan district of Nepal. All pediatric patients 0 to 16 years of age meeting the inclusion criteria will form the study population. In the pediatric department of BEH, children aged 0 to 16 years are being examined as per the hospital policy.

The inclusion criteria are all pediatric patients 0 to 16 years of age advised for at least 3 follow-up visits within a 6-month period at BEH, parents or guardians of children who own a mobile phone or have daily access to a phone and are able to use the SMS text feature on these phones, and parents willing to enroll their children in the study.

The exclusion criteria are children who require fewer than 3 follow-up visits, children with ocular conditions requiring daily follow-up visits (because it is not feasible to send the reminder phone call and SMS text for daily follow-up), children who have already been treated and are under regular follow-up, children with ocular conditions requiring follow-up beyond 6 months, parents or guardians of the children who are not willing to participate in the study, and those who have been called but do not answer after 3 attempts

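### A failed reminder SMS goes to a second recorded number, but a failed reminder call leads, on an inconsistent attempt count, to exclusion from the reminder arm only

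*Protocol article*

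**What the plan says.** The relevant text of the protocol article is in two sections.

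**SMS Text and Phone Call Reminder Group**
- Schedule: "They will receive an SMS text 3 days prior to and a phone call 1 day prior to their scheduled follow-up visits".
- Undelivered SMS: it is re-sent, and if it still fails, "then a message will be sent to the next phone number (if available) as recorded in the proforma during the interview".
- Unanswered call: "calls will be repeated at least 3 times if the phone is not answered in the first instance".
- Consequence: "If the call is not answered even after 3 attempts, the participant will be excluded from the study".

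**Study Design and Setting**
- Phone access at entry is set for "parents or guardians of children who own a mobile phone or have daily access to a phone", who must also be able to use SMS.
- The exclusion criteria list "those who have been called but do not answer after 3 attempts".

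Reminder calls are described only for the reminder group, and the control-group section rules reminders out for that arm. The Multivariate Analysis section makes an intention-to-treat analysis conditional on need.

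**The concern.** The SMS and the call are two halves of one intervention, made by one assistant from one proforma, but their contact rules differ. The SMS rule uses a second number when there is one. The call rule, as written, runs from repeated attempts straight to exclusion, with no step at which another number would be tried.

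The consequence is also heavier for the call. No penalty is stated for an SMS that never arrives, while an unanswered call ends the child's participation. The trigger is therefore worth getting right, and its count is not consistent.

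At stake are avoidable losses after allocation in the reminder arm alone. They cost participants, and they may select the more contactable families into that arm's completion rate. The introduction hypothesises a rise of only 3 percentage points from reminders (22% to 25%), so even a small selection effect matters.

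**Working it through.** **1. The two contact rules side by side**

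| Step | SMS | Call |
|---|---|---|
| First failure | Re-sent | Repeated |
| Further failure | Next recorded number, if there is one | No step stated |
| Final consequence | None stated | Participant excluded |

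**2. The attempt count**

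One unanswered call followed by at least 3 repeats is 1 + 3 = at least 4 calls. The next sentence, and the exclusion criterion, act after 3. A family that has not answered call 3 is excluded under one wording and due another call under the other.

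**3. Direction of the harm**

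Let *p* be the true completion rate among all children allocated to the reminder arm, *x* the share excluded for not answering, and *q* the completion rate those children would have had. The rate observed among those kept is (*p* − *xq*)/(1 − *x*). Take *p* = 25%, the plan's hypothesised reminder rate. The values of *x* and *q* are assumptions.

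| *x* | *q* = 0 | *q* = 10% | *q* = 25% |
|---|---|---|---|
| 5% | 26.3% | 25.8% | 25% |
| 10% | 27.8% | 26.7% | 25% |
| 20% | 31.25% | 28.75% | 25% |

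Example: (0.25 − 0.10 × 0)/0.90 = 27.8%. With 10% excluded, the shift is 0 to 2.8 points, against a hypothesised effect of 3 points.

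**4. What a second number could recover**

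The plan gives no figure on this point to reproduce. Its 264 participants serve only as the denominator: 264/3 = 88 per arm. Assume first-number failure *a* = 5%, a second number for *v* = 50% or 80% of families, and a 70% answer rate on it.

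Failure per visit = *a*(1 − 0.7*v*):
- *v* = 50%: 0.05 × 0.65 = 3.25%
- *v* = 80%: 0.05 × 0.44 = 2.2%

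*Upper bound: every child is due three calls.* Any failure = 1 − (1 − *f*)³, where *f* is the failure per visit:
- No fallback: 14.3%, or 12.6 of 88
- With fallback: 9.4% or 6.5%, or 8.3 or 5.7 of 88
- Gain: about 4 to 7 children

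*Lower case: 25% reach a second call and none a third.* This follows the second dry run, where 3 of 12 reminder children attended the first follow-up and none a later one. Any failure = *f* + (1 − *f*) × 0.25 × *f*:
- No fallback: 0.05 + 0.95 × 0.25 × 0.05 = 6.2%, or 5.4 of 88
- With fallback: 4.0% or 2.7%, or 3.6 or 2.4 of 88
- Gain: about 2 to 3 children

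With *a* = 10%, failure per visit falls to 6.5% or 4.4%, and the three-call bound falls from 27.1% to 18.3% or 12.6%.

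**5. What remains after the change**

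Count only the first-visit call, with *q* = 0 and *p* held at 25%. The observed rate is 26.3% when *x* = 5%, 0.25/0.9675 = 25.8% when *x* = 3.25%, and 0.25/0.978 = 25.6% when *x* = 2.2%. The distortion shrinks but does not vanish.

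**The case against.** **The missing fallback is read from silence.** The article does not say which number is rung on repeat attempts. It condenses a fuller protocol, and the appendices with the proforma and the SMS and call formats are not shown. This stands in part: an unpublished call rule cannot be ruled out. But the article does state what follows the unanswered attempts, and any fallback kept elsewhere would have to be reconciled with that sentence.

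**The attempt count is only loose wording.** The SMS rule has the same pattern (three re-sends, then a step after three attempts), so attempts may mean repeats. That is a fair reading of the reminder section. It does not settle the exclusion criterion, which counts attempts with no mention of repeats, and the words at least leave the number open. A count that ends participation should not need interpretation.

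**A second number may reach the wrong person.** A call counts as complete when the respondent takes it, and a second number may reach a relative. These families will normally have been sent the SMS as well. Both remarks limit the gain, and so does the fact that a second number will not exist for everyone.

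**A stronger reading: missed calls dilute the intervention.** A reader might infer that unreached families stay in without the call and shrink the contrast. The documents do not support this. Such families are excluded, so they cannot dilute the rate among those kept. If they attend less, excluding them moves the observed rate up.

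**Another stronger reading: about 14% of the arm is at risk.** That figure assumes three calls for every child, whereas the Compliance to Follow-up section considers a child for the next visit only after attending the one before. It is an upper bound resting on an assumed failure rate.

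**Conclusion.** The point holds as a minor matter of delivery and wording. The article gives the SMS a second-number fallback and states none for the call, and the count that triggers exclusion is inconsistent. The harm is avoidable loss after allocation in the reminder arm only, with possible upward selection in its completion rate.

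The size is not known. Under the 5% assumption a fallback would keep about 2 to 7 of 88 children. The upward shift in the observed rate is zero if non-answerers complete as often as the others. The direction depends on their attending less, which is plausible but not documented.

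A fallback number would not by itself remove the bias from the exclusion rule. That rule is the weightier problem, because it conditions on response to the intervention in one arm while intention-to-treat is only conditional.

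**What to change.** 1. Before a call is classed as unanswered, ring the next number recorded in the proforma, where there is one, as is already done for the SMS.
2. State a single attempt count, in the same words, in the exclusion criteria and in the reminder-group section, and say whether it applies per number or in total.
3. Log at each visit which number was reached and by which attempt, so that delivery can be reported.
4. Keep children who are still unreached in their allocated group for analysis, and record the unanswered call as delivery data. The first three steps shrink the one-arm loss; this one addresses what is left.

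**Cost.** A few extra calls by the same assistant, using numbers already collected. A second number may sometimes reach a relative, so the log should show who answered. The article reports 154 of 264 participants already enrolled as of September 2021. A change from then on makes delivery differ slightly between early and late participants, so its date should be recorded and reported.

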### Sample Size

Bonferroni correction (level of significance *P*=.05; k=3 comparisons) was adopted for sample size calculation with consideration to the proportion of attendance in counseling (p1) and reminder SMS texts and phone calls (p2) as 50% (0.5) and 25% (0.25), respectively. An estimated sample size of 264 pediatric patients will be targeted with an adjusted significance level of .02, 80% power, and 10% loss to follow-up.

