#### Routine Standard Care Group/Control Group

In this group, the children will undergo visual acuity testing and refraction by an optometrist. The pediatric ophthalmologist will perform detailed ocular examination and advise necessary investigations to diagnose and formulate a treatment plan. Basic counseling will be done by the consultant regarding the ocular condition, treatment, and need for follow-up. No additional counseling or reminders will be performed for these patients. They will be discharged from the department and advised for follow-up as per the hospital protocol. The follow-up schedule as per the hospital protocol for common ocular conditions is shown in Table 1.

**Table 1 table1:** Schedule for follow-up for different ocular conditions.

Ocular condition	Recommended guidelines for follow-up [11]
Congenital naso-lacrimal duct obstruction	Once every 4 weeks
Keratitis	Depending on severity, at least once a week
Allergic conjunctivitis	Once every 2 weeks
Ocular injury	Depends on severity of injury, daily to once a week
Pediatric cataract	Once every 2 weeks
Strabismus	Once every 2 weeks
Amblyopia	Once every 4 weeks
Retinopathy of prematurity	Once every 2 weeks

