### Study Procedure

All participants will be enrolled in the study after fulfilling the inclusion criteria and administering informed consent. Recruitment will be conducted over a 6-month period. Participants will be assigned a unique code which will be a 6-digit number generated by using the last 3 digits of the patient’s medical record number and the last 3 digits of the parent’s or guardian’s mobile phone number. The participants will be entered into 3 groups, such that the first patient will be enrolled to the routine standard care group, the second to the counseling group, and the third to the group of SMS texts and phone call reminders. The same sequence will be followed for every participant until the required sample size has been attained. Before the actual start of the recruitment, 2 dry runs were conducted to understand the flow of the patients and logistics of the study.

After registration, the patient will be guided by the Outpatient Department (OPD) facilitator to the vision and refraction room and then to the consultant room. After ocular examination, treatment and follow-up advice, the consultant will paste a colored sticker on the patient’s file to indicate the potential study participant. There will be a separate and dedicated place for the pediatric ophthalmologist, assistant, and the counselor (Multimedia Appendix 1).

Patients with a colored sticker on their OPD file will be referred to the assistant room. The assistant will take the written consent from the children in an assent form (if 9 years or older) and from their parents or guardians in a consent form after explaining the study and group and selection to them (Multimedia Appendix 2 and 3).

A unique number will be allotted to the patient (generated through the medical record number and mobile phone number of the patient). The unique ID of the participants will be recorded in the proforma and on the examination file by the assistant. He will fill all the details in the proforma (Multimedia Appendix 4) and also enter the details in a Microsoft Excel sheet.

The patients assigned to counseling will be sent to the counselor. The counselor will conduct a counseling session based on the ocular condition and follow-up plan. Counseling will be done as per the prescribed counseling protocol. After counseling, the counselor will provide the information leaflets, and the patient will be asked to visit the optical dispenser or pharmacist.

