#### Multivariate Analysis

Multivariate logistic regression analysis will be performed to adjust for the simultaneous effects of multiple factors on the outcome variable. The criteria for inclusion of factors in the multivariate analysis are to include all variables from the univariate analysis with a *P* value of .1 along with all the variables of known importance. To assess the importance of each variable included in the model, the Wald statistic for each variable will be used.

Before the multivariate analysis is conducted, the association among independent variables will be checked by a chi-square test. For independent variables having more than 2 categories, dummy variables will be created. All the variables meeting the above selection criteria will be entered one by one, starting with the highly significant factors from the univariate analysis. The overall significance of independent variables in the model will be assessed by likelihood ratio test (G statistic). Selection of the final model will be based on parsimony, biological interpretability, and statistical significance. The parameters of the logistic regression model will be estimated by the maximum likelihood method. The adjusted ORs and their 95% CIs will be computed using the estimates of parameters of the final model. The dependent variable will be dichotomous: either compliance with the follow-up instruction has increased, or it has remained changed (no difference) from before the intervention study to after it. The final model will be tested for goodness of fit by Hosmer- Lemeshow chi-square (*Χ*^2^) statistic. *P* values will be noted to assess the model fit. Imputation and intention to treat analysis will also be conducted (if required).

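### Reminder-group children are excluded after allocation when the reminder call goes unanswered, a rule that can act in no other group and leaves the primary comparison non-comparable

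*Protocol article*

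**What the plan says.** The rule appears twice in the protocol article. The section on the SMS text and phone call reminder group states: "If the call is not answered even after 3 attempts, the participant will be excluded from the study". The exclusion criteria under Study Design and Setting also list "those who have been called but do not answer after 3 attempts".

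The timing is given in the reminder-group section: "They will receive an SMS text 3 days prior to and a phone call 1 day prior to their scheduled follow-up visits". Consent and group assignment happen at the first visit (Study Procedure), so every reminder call comes after allocation.

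The other groups have no matching step. For controls the article says "No additional counseling or reminders will be performed for these patients". Counseling is given in person: "The counselor will deliver verbal counseling for all participants in all follow-up visits". No call to that group is described.

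The primary outcome is the proportion completing all three follow-up visits, by group (Outcomes). A child who does not come within the 2-day window is not compliant (Compliance to Follow-up).

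Two other statements bear on the analysis set. Under Multivariate Analysis: "Imputation and intention to treat analysis will also be conducted (if required"). Record Maintenance says group assignment holds whether or not the intervention is received.

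**The concern.** An exclusion triggered by an event that can occur in only one group changes that group's denominator and leaves the others untouched. Families who would not answer a call presumably exist in all three groups. In the control and counseling groups nobody identifies them, so they stay in and count as failures if they miss a visit. In the reminder group they are removed, and the groups are no longer the ones that allocation formed.

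Failure to reach a family is also part of how a reminder service performs. A family whose text message arrived but who missed the call has received part of the intervention and is still removed. The Discussion says that an effective intervention would become hospital policy, and for that decision the relevant rate is the one among all families offered reminders. The cost per attendance in the cost-effectiveness analysis would shift too if excluded children are left out of it.

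**Working it through.** **Does the rule act in one group only, and after allocation?** Yes on both counts. The only calls described are reminder calls, made the day before a visit, to the reminder group. The entry among the exclusion criteria therefore cannot work as an eligibility screen.

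**Does anything cancel it?** No. Intention to treat is described as additional and conditional, so it is not fixed as the primary analysis. The Record Maintenance statement sits uneasily with the exclusion but does not override it.

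**Inputs for the size of the effect**
- p = 22%, the plan's baseline, taken as the true rate in both groups (no true reminder effect).
- Hypothesised reminder rate: 25% (end of the Introduction).
- u = share of reminder-group children excluded for not answering. Not in the document; assumed.
- r = non-answerers' compliance divided by answerers' compliance. Not in the document; assumed.

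**Formula.** If answerers comply at rate q, the whole group's rate is p = (1 − u)q + u·r·q. After exclusion only answerers are analysed, so the reported rate is

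q = p / [(1 − u) + u·r].

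Examples: u = 12%, r = 0 gives 0.22/0.88 = 25.0%; u = 20%, r = 0.5 gives 0.22/0.90 = 24.4%.

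| u | r = 0 | r = 0.5 | r = 1 | r = 1.5 |
|---|---|---|---|---|
| 5% | 23.2% | 22.6% | 22.0% | 21.5% |
| 10% | 24.4% | 23.2% | 22.0% | 21.0% |
| 12% | 25.0% | 23.4% | 22.0% | 20.8% |
| 20% | 27.5% | 24.4% | 22.0% | 20.0% |
| 30% | 31.4% | 25.9% | 22.0% | 19.1% |

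To produce the full shift from 22% to 25%, u must be 1 − 0.22/0.25 = 12% if non-answerers never comply, or 2 × 12% = 24% if they comply at half the answerers' rate.

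**Effect on false positives.** The planned total of 264 in three equal groups gives 264/3 = 88 each. I used the plan's adjusted level of .02 (taken as two-sided), a normal approximation, 88(1 − u) children at rate q against 88 controls at 22%, the pooled standard error for the critical value and the unpooled one for the probability of rejection. For u = 20%, r = 0:
- reminder group 70.4 children at 27.5%, pooled rate 38.72/158.4 = 24.4%;
- pooled SE 0.0687, unpooled SE 0.0692;
- upper tail: (2.326 × 0.0687 − 0.055)/0.0692 = 1.52, probability about 6.5%; the lower tail adds about 0.1%; total 6.6%.

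Against a nominal 2.0%, the results for u = 10%, 20% and 30% are 2.9%, 6.6% and 15.5% at r = 0, and 2.2%, 2.9% and 4.1% at r = 0.5.

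**Dependence on the baseline.** The Introduction's 22% is the share who came for one or more visits. The primary outcome needs all three, so its rate may be lower. The relative inflation, 1/[(1 − u) + u·r], does not depend on p, but the shift in points does. With an illustrative all-three rate of 5%, u = 12% and r = 0 give 0.05/0.88 = 5.7%, a shift of 0.7 points instead of 3.

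**The case against.** **Direction.** A reader might infer that the rule must inflate the reminder rate. The document does not establish that. It needs r below 1; at r = 1 there is no bias in the rate, and above 1 the rate falls. The rule also applies at every visit, so it can remove a child who has already attended one or two visits and is more likely than average to finish. Upward bias remains the likelier direction, because an unreached family missed the call and may be disengaged, but this is an inference.

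**Size.** A reader might infer that the bias equals the hypothesised effect. That holds only for particular assumed pairs of u and r. Eligibility requires a phone or daily access to one and the ability to use text messages, and calls are repeated; both may keep u small. At u = 5% the shift is at most 1.2 points on the 22% baseline. This point stands, but it does not remove the asymmetry.

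**Imputation.** A reader might infer a second upward bias from imputing attendance. The document does not say what would be imputed; missing covariates are a natural reading under a regression heading, and imputation applied to all groups need not favour one of them.

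**The 10% allowance.** A reader might take "80% power, and 10% loss to follow-up" as a further error, because non-attendance is itself the outcome. It is a sample-size inflation that could cover withdrawals or these very exclusions, and it causes no bias.

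**An unseen analysis plan.** A fuller document might define the analysis sets. But the article itself fixes removal from the study, so this is a stated rule and not a detail left for later.

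**Conclusion.** The point holds as a design fault in a primary comparison. The article prescribes a post-allocation exclusion that only the reminder group can incur, and the conditional mention of intention to treat does not undo it. That conclusion rests on the text alone.

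The bias is likely upward, on the assumption that non-answerers comply less than answerers. Its size cannot be determined from the document. On the 22% baseline with no true effect, u from 5% to 20% gives reported rates of 23.2% to 27.5% at r = 0, 22.6% to 24.4% at r = 0.5, and 22% at r = 1. Since the plan hopes to move the rate from 22% to 25%, plausible values could account for some or all of that effect. Even if the rate happened to be unbiased, the comparability that allocation was meant to give would be lost. The plan should be corrected before analysis.

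**What to change.** 1. Delete the unanswered-call exclusion from the exclusion criteria and from the reminder-group section, and reconcile both with Record Maintenance and Multivariate Analysis.
2. State that the primary analysis is intention to treat: every allocated child in the assigned group, with a visit not attended within the window counted as non-compliant.
3. Record call and SMS delivery for each visit as process data, and report the non-answer share.
4. Report an analysis restricted to families reached by phone only as secondary.
5. Reinstate children already excluded where their attendance was recorded or can be retrieved, and report how many cannot be. Record Maintenance covers all follow-up visits of participants, but does not say that tracking continues after exclusion. Excluded children may also have stopped receiving later reminders, which should be reported.

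The cost is a protocol amendment, some checking of records, and possibly a less favourable reminder rate. At the last report 154 of 264 children had been enrolled, so the change could be made before the data were complete.
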